## Abstract

**Background:**

Amnestic mild cognitive impairment (aMCI) is a pre-dementia condition associated with declined cognitive function dominated by memory impairment. The occurrence of aMCI is associated with the gut-brain axis. Previous studies have shown cognitive improvements in MCI after acupuncture treatment. This study evaluates whether acupuncture can produce a therapeutic effect in patients with aMCI by modulating the gut-brain axis.

**Methods and design:**

This is a prospective, parallel, multicenter randomized controlled trial. A total of 40 patients with aMCI will be randomly assigned to an acupuncture group (AG) or a waiting-list group (WG), participants in both groups will receive health education on improving cognitive function at each visit, and acupuncture will be conducted twice a week for 12 weeks in the AG. Another 20 matched healthy volunteers will be enrolled as normal control. The primary outcome will be the change in Alzheimer’s Disease Assessment Scale-cognitive scale score before and after treatment. Additionally, functional magnetic resonance imaging data, faeces, and blood will be collected from each participant to characterize the brain function, gut microbiota, and inflammatory cytokines, respectively. The differences between patients with aMCI and healthy participants, and the changes in the AG and WG groups before and after treatment will be observed. Ultimately, the correlation among brain function, gut microbiota, inflammatory cytokines, and clinical efficacy evaluation in patients with aMCI will be analyzed.

**Discussion:**

This study will identify the efficacy and provide preliminary data on the possible mechanism of acupuncture in treating aMCI. Furthermore, it will also identify biomarkers of the gut microbiota, inflammatory cytokines, and brain function correlated with therapeutic effects. The results of this study will be published in peer-reviewed journals.

**Clinical trial registration:**

http://www.chictr.org.cn, identifier ChiCTR2200062084.

## Introduction

1.

Mild cognitive impairment (MCI) refers to a transitional phase between cognitive changes of normal ageing and dementia, which is often seen in Alzheimer’s disease (AD) (1). It is characterized by a decline in memory, language and executive function (2). The prevalence of MCI varies between 10% and 20% in adults aged ≥65 years and increases with age (3), and approximately 5 million individuals in the United States aged ≥65 years have MCI (4). The proportion of people with MCI increased from 11.9% in people aged 60–69 years, 19.3% in those aged 70–79 years, and 24.4% in those aged 80–89 years in China (5). The World Health Organization has reported that more than 245 million people in the Western Pacific Region are >65 years old, with this number projected to double by 2050 (6). Thus, the number of patients with MCI tends to increase.

MCI is classified into amnestic MCI (aMCI) and non-amnestic MCI (naMCI) (2). As the most common subtype of MCI, aMCI refers to a syndrome of cognitive decline dominated by memory impairment, with preserved independent functional abilities (7). Individuals with aMCI are more likely to deteriorate to dementia than the age-matched normal population or people with naMCI (8, 9). Because of the progressive decline in cognition, aMCI markedly affects the patient’s quality of life and imposes a substantial financial burden on families and society (10). In the United States, patients with aMCI have significantly less annual household income (average of $29,754) compared to individuals with normal cognition (average of $45,500) (11). This makes aMCI a global concern that needs urgent attention and solutions.

Early recognition and effective intervention for aMCI are critical for slowing down disease progression (4). Based on the updated guideline of the American Academy of Neurology, no pharmacological or dietary agents have been proven to improve the clinical symptoms or delay the progression of aMCI (12). The efficacy of traditional drugs is insufficient (13). For example, cholinesterase inhibitors have limited effects on cognitive function over the short-term but substantially high adverse effects (14). Other management options recommended for aMCI, such as lifestyle changes, aerobic exercise and social engagement, also seem unsatisfactory (3). Therefore, alternative interventions to manage aMCI have become of interest.

As a traditional Chinese medicine (TCM) component, acupuncture has been applied to various neurological diseases for thousands of years. According to TCM theory, acupuncture involves inserting needles into acupoints to adjust Qi and blood of meridians and balance yin and yang throughout the body, thus normalizing the patient’s health status (15). Abundant randomized controlled trials (16, 17) and systematic reviews/meta-analyses (18, 19) have shown that acupuncture can be used to treat MCI. Xu et al. (20) found that the effect of acupuncture on MCI was better than western medicines. Additionally, our previous systematic review (18) indicated that acupuncture is an effective therapy for overall cognitive function improvement in patients with MCI. Acupuncture seems to be a promising complementary therapy for aMCI; however, the underlying mechanisms of acupuncture are still under debate.

Previous studies found that patients with aMCI have changes in brain structure and function, including reduced cortical thickness, and abnormal activity and functional connectivity in specific brain regions (21, 22). In recent years, evidence has established that aMCI occurrence is associated with gut microbiota alteration and neuroinflammatory response (23). Changes in gut microbiota and its metabolites interact with human brain development and cognitive function (24, 25). The dynamic bidirectional connection pathway between the gastrointestinal tract and the nervous system is termed the “gut-brain axis” (26). Gut microbiota taxa could be used as key early indicators of cognitive performance in patients with aMCI (23). Sodium oligomannate has been demonstrated to reverse cognitive impairment by remodelling the gut microbiome and limiting neuroinflammation (27). Based on this, gut microbiome dysbiosis and neuroinflammation may be critical factors contributing to cognitive impairment in patients with aMCI. In recent years, researchers found that acupuncture improved cognition in animal models of AD by modulating the microbiota-gut-brain axis (28–30). Additionally, a review demonstrated that acupuncture exerts an anti-neuroinflammation effect through multiple pathways (31). Thus, we hypothesise that acupuncture may improve the cognitive function of patients with aMCI by regulating the gut-brain axis.

Evidently, the gut-brain axis may play a crucial role in the aMCI pathogenesis. To our knowledge, no study has been conducted to elucidate the underlying mechanisms of acupuncture for aMCI based on the gut-brain axis. Therefore, we designed a parallel-arm, randomised, controlled clinical trial to explore the therapeutic mechanisms of acupuncture for aMCI from the perspective of gut-brain modulation.

## Objectives

2.

To observe the efficacy and safety of acupuncture in patients with aMCI;To investigate whether acupuncture can regulate brain function by affecting the gut microbiome and expression of inflammatory cytokines in the gut-brain axis, thus playing a role in improving cognitive function in patients with aMCI.

## Design and methods

3.

### Trial design and setting

3.1.

This is a parallel-designed, prospective, assessor-blinded multicentre (*n* = 4) randomised controlled study to explore whether acupuncture can improve clinical symptoms of patients with aMCI by regulating the gut-brain axis. Forty patients with aMCI will be randomly and evenly assigned to either the acupuncture group (AG) or the waiting-list group (WG). Various scales will be assessed, functional Magnetic Resonance Imaging (fMRI) scans will be performed, and blood and faeces samples will be collected from both groups of patients before and after the intervention. In addition, 20 healthy participants will be recruited as normal control, and relevant tests and examinations will be conducted at enrollment. Cognitive-related scale, daily-living ability scale, emotion scale, mental behaviour scale and sleep scale will be used to observe the changes in clinical symptoms of patients with aMCI and to identify the therapeutic effect of acupuncture on aMCI. The gut-brain interaction characteristics of patients will be determined, and the regulatory effect of acupuncture on gut microbiota, inflammation cytokines and brain function will be explored. Subsequently, the correlation analysis of clinical efficacy can be related to gut microbiota composition, inflammation cytokines and brain function. The flow chart of trial procedures is displayed in Figure 1, and the study schedule is depicted in Table 1. The trial will be conducted at four sub-centres (West China Hospital of Sichuan University, Sichuan Provincial People’s Hospital, Chengdu Fourth People’s Hospital, and Sichuan Provincial Rehabilitation Hospital). The study protocol reporting follows the Standard Protocol Items: Recommendations for Interventional Trials (SPIRIT) guidelines and checklist (32).

**Figure 1 fig1:**
[figure not shown]
Flow chart of the trial procedures.

**Table 1 tab1:** Schedule of enrollment, intervention, and assessments.

Timepoint	Study period				
	aMCI patients				Healthy participants
	Baseline	Treatment phase			Baseline
	0-week	Week 1	→	Week 12	**0-week**
Enrollment:					
Eligible screen	X				X
Informed consent	X				X
Randomization	X				
Interventions:					
Acupunctue group		X	→	X	
Waiting-list group		X	→	X	
Examinations:					
fMRI scan	X			X	X
Blood detection	X			X	X
Feces detection	X			X	X
Assessments:					
ADAS-cog	X			X	X
AVLT-H	X			X	X
MoCA-B	X			X	X
FAQ	X			X	X
HAMD	X			X	X
HAMA	X			X	X
MBI-C	X			X	X
PSQI	X			X	X
Adverse events		X	→	X	

aMCI, amnestic mild cognitive impairment; ADAS-cog, alzheimer’s disease assessment scale-cognitive subscale; AVLT-H, auditory verbal learning test – huashan; MoCA-B, montreal cognitive assessment - basic; FAQ, functional activities questionnaire; HAMA, hamilton anxiety scale; HAMD, hamilton depression scale; MBI-C, mild behavioral impairment-checklist; PSQI, pittsburgh sleep quality index; fMRI, functional magnetic resonance imaging.

### Participants

3.2.

Eligible participants will be recruited from clinical centres, communities and welfare institutes in Sichuan province. Written informed consent will be obtained before participation if the participants meet the inclusion criteria.

### Eligibility criteria

3.3.

#### Inclusion criteria for patients with aMCI

3.3.1.

Patients who meet the following criteria will be included: (1) diagnosis of aMCI according to the Jak/Bondi 2014 diagnostic criteria (33); (2) right-handedness and age between 50 and 80 years; (3) disease course ≥6 months; (4) a Clinical Dementia Rating (CDR) score of 0.5; (5) a Hachinski Incheinic Score (HIS) ≤ 4; (6) education level ≥ 8 years (including vocational education); (7) volunteering to cooperate and signing an informed consent form; and (8) no contraindications to MRI scanning, such as pacemaker implantation, metal fixed dentures.

#### Exclusion criteria for patients with aMCI

3.3.2.

Patients who meet any of the following criteria will be excluded: (1) receiving treatment that interferes with cognitive function (e.g., management of acute psychotic episodes, such as memantine, rivasmine, donepezil); (2) a history of neurological conditions affecting cognitive function confirmed by examination, except in patients with suspected early AD, including Parkinson’s disease, vascular dementia, brain tumour, traumatic brain injury, or other diseases which might lead to neurological injury and abnormal brain structure; (3) presence of a systemic diseases that could cause cognitive decline, such as anaemia, Hashimoto’s encephalopathy, metabolic encephalopathy, hepatic encephalopathy, renal encephalopathy; (4) infection, other focal injury, multiple or important brain memory area infarcts, or severe leukodystrophy (Fazekas score ≥ 3) indicated by brain MRI; (5) a history of tumour, psychiatric illness (e.g., bipolar disorder, schizophrenia) or severe depression (Hamilton Depression [HAMD] scale score ≥ 24) and anxiety (Hamilton anxiety [HAMA] scale score ≥ 29); (6) haemorrhagic disease, bleeding tendency or severe skin infection; (7) severe drug dependence, smoking, drug or alcohol abuse; (8) pregnant, potentially pregnant, or lactating females; (9) receipt of any acupuncture therapy or participation in other clinical trials during the 6 months prior to enrolment; and (10) regularly use of probiotics, prebiotics, or antibiotics.

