#### Exclusion criteria for healthy participants

3.3.4.

Participants who meet any of the following criteria will be excluded from the normal control group: (1) claustrophobia; (2) severe cranial anatomical asymmetry or definite lesions found in MRI; (3) regularly use of probiotics, prebiotics, or antibiotics; or (4) participation in other clinical trials.

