**Figure 2 fig2:**
[figure not shown]
Locations and manipulations of acupoints selected in this study: GV 20 (Baihui), 5 cun directly above the midpoint of the anterior hairline, at the midpoit of the connecting the apexes of the two auricles. Subcutaneous insertion to a depth of 0.5-1 cun with manipulation for the deqi. GV 24 (Shenting), 0.5 cun directly above the midpoint of the anterior hairline. Subcutaneous insertion to a depth of 0.3-0.5 cun with manipulation for the deqi. EX-HN 18 (Anmian), at the neck, the midpoint of the line between GB20 (Fengchi) and TE 17 (Yifeng). Subcutaneous insertion to a depth of 0.5-1 cun with manipulation for the deqi. HT 7 (Shenmen), at the ulnar end of the transverse crease of the wrist, in the depression on the radial side of the tendon of m. flexor carpi ulnaris. Subcutaneous insertion to a depth of 0.3-0.5 cun with manipulation for the deqi. KI 3 (Taixi), posterior to the medial malleolus, in the depression between tip of the medial malleolus and tendo calcaneus. Subcutaneous insertion to depth of 0.5-1 cun with manipulation for the deqi.

Patients in the WG will not undergo acupuncture treatment during the observation period, and they will be informed that 24 free acupuncture sessions can be provided to them after observation.

Both groups will receive 10–15 min of aMCI-related health education at each visit to improve their cognitive function. The health education content is referred to in the *Dietary and lifestyle guidelines for the Prevention of Alzheimer’s Disease,* published in *Neurobiology of Aging* in 2014 (39). During the trial, patients will be allowed to receive basic treatment, such as blood pressure control, glucose control, and other supportive care. The time, dose, frequency, and response to treatment will be recorded. Participants will also be advised to avoid using other medications that affect cognitive function or acupuncture, massage, application, etc. The clinician will formulate a corresponding treatment plan and make detailed records if the symptoms are severe.

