#### Changes in gut microbiota

3.8.3.

Faecal samples of all patients will be collected at the beginning and end of the intervention. In the morning, participants will be requested to collect mid-medial faecal samples (at least 2 g) using a disposable stool kit. After the samples are obtained, they will be stored at − 20°C freezers, sent to the laboratory, and placed in the refrigerator at −80°C within 24 h for preservation. We will use a metagenomic sequencing technique to determine the gut microbiota of participants. The DNA of gut microbiota from faecal samples will be extracted using the kit. Subsequently, we will establish a DNA library (paired-end; insert length 350 bp of each sample) according to the manufacturer instructions of Illumina, and conduct high-throughput sequencing using paired-end readings of length 2 × 100 bp. Subsequently, cluster analysis, assembly and annotation of metagenomic data will be conducted. Finally, the annotation, composition, differences, and comparison of species in the intestinal microbiota of patients will be analysed, and the similarities and differences in the diversity and abundance of gut flora will be compared between the AG and WG.

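### The microbiota exclusions reach only undefined 'regular' use of antibiotics, probiotics or prebiotics, with no look-back window, so recent short-course users are eligible

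*Protocol article*

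**What the plan says.** Section 3.3.2, item 10, excludes patients for "regularly use of probiotics, prebiotics, or antibiotics". Section 3.3.4 applies the same wording to healthy controls: "3) regularly use of probiotics, prebiotics, or antibiotics". Neither defines regular use or gives a period before sampling. The item just before it in the patient list does both, excluding "receipt of any acupuncture therapy or participation in other clinical trials during the 6 months prior to enrolment".

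On sampling, section 3.8.3 states: "Faecal samples of all patients will be collected at the beginning and end of the intervention". Healthy controls give one sample, at enrolment (section 3.6.2).

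During the 12 weeks, section 3.6.1 says that "patients will be allowed to receive basic treatment, such as blood pressure control, glucose control, and other supportive care", and adds: "The time, dose, frequency, and response to treatment will be recorded". Patients are also "advised to avoid using other medications that affect cognitive function or acupuncture, massage, application, etc". Antibiotics, probiotics and prebiotics are not named there. Section 3.8.1 records concomitant medication, and section 3.8.5 evaluates patients' drug use at the beginning and end of the intervention.

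**The concern.** By listing these agents as exclusions for both patients and controls, the protocol treats them as a threat to the microbiota data. A rule limited to regular use leaves out the single recent course, and the four centres have no common definition of regular to apply.

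The gut microbiome is part of the trial's second objective (section 2). Each patient gives only two stool samples and each control one, so an exposed sample cannot be averaged out over repeated measurements. The tests in section 3.11 are unadjusted. Three analyses are at stake: the comparison of the acupuncture group (AG) with the waiting-list group (WG), the comparison of patients with healthy controls, and the regression relating microbiota to cytokines, brain function and clinical efficacy.

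**Working it through.** **Step 1: the criteria side by side.** Item 9 of section 3.3.2 covers any acupuncture within a stated 6 months. Item 10 covers regular use with no period. A patient who finished one antibiotic course days before the baseline sample meets no exclusion as written, and the same holds for a control under section 3.3.4.

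**Step 2: what would identify an exposed sample.**
- Patients: sections 3.6.1, 3.8.1 and 3.8.5 provide for recording medication, in 3.8.5 at the same two times as stool collection. A prescribed antibiotic should be traceable. Over-the-counter or dietary probiotics and prebiotics may not be entered as drug use.
- Controls: section 3.6.2 names general information and cognitive results, with medical history used to establish eligibility. No drug-use record is stated.
- Handling: the article gives no restriction, sampling delay or analysis rule for exposed samples.

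**Step 3: illustrative size.** The plan has no figure to reproduce. The 20 per group in section 3.5 comes from precedent, without an effect size, SD or power. Exposure rates and shifts below are assumptions.

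With n = 20 per arm and exposure probability p near a given sample, P(at least one exposed in an arm) = 1 − (1 − p)^20. The probability that the arms differ by two or more exposed patients is the sum of the products of the two binomial(20, p) probabilities over all pairs of counts differing by at least 2.

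| Assumed p | Expected exposed per arm | P(at least one in an arm) | P(arms differ by 2 or more) |
|---|---|---|---|
| 2% | 0.4 | 33% | 8% |
| 5% | 1 | 64% | 25% |
| 10% | 2 | 88% | 42% |
| 20% | 4 | 99% | 55% |

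For a fraction f of a group exposed, each shifted by s SD, the group mean moves by f × s and its SD becomes sqrt(1 + f(1 − f)s²). With f = 2/20 = 0.1:
- s = 2: mean shift 0.2; SD = sqrt(1 + 0.09 × 4) = 1.17, up 17%.
- s = 3: mean shift 0.3; SD = sqrt(1 + 0.09 × 9) = 1.35, up 35%.

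**Step 4: against the trial's own precision.** At two-sided 0.05 and 80% power (assumed; normal approximation), the detectable difference with 20 per arm is (1.960 + 0.842) × sqrt(2/20) = 0.89 SD. If only one arm has the two exposed patients, the expected t is:
- s = 2: 0.2 / sqrt((1.36 + 1)/20) = 0.58.
- s = 3: 0.3 / sqrt((1.81 + 1)/20) = 0.80.

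If both arms are 10% exposed, there is no shift between them, but the detectable difference grows to 0.886 × 1.166 = 1.03 SD (s = 2) or 0.886 × 1.345 = 1.19 SD (s = 3).

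**Step 5: patients against controls.** The bias is (f_patients − f_controls) × s. With 10% against 0% it is 0.2 to 0.3 SD; with equal rates it is zero. Randomisation does not bring these rates together.

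**The case against.** The strongest reply is that the protocol already screens for these agents in both populations and records patients' medication, in section 3.8.5 at the very times stool is collected. A reader might infer that nothing covers use during the 12 weeks, or that exposed patients are necessarily analysed as if unexposed. The documents do not support either reading. For patients, prescribed antibiotics should be identifiable afterwards.

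Second, this is a condensed article. A rule for exposed samples or a sensitivity analysis may be in the full protocol, the analysis plan or the clinical study manual mentioned in section 3.10. That stands, so the absent handling rule is not a defect in itself. It does not excuse the eligibility wording, which the article sets out item by item.

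Third, a reader might infer that one or two exposed samples could create or hide an AG–WG difference. That is too strong. Exposure before baseline is balanced in expectation by random allocation, and the documents give no reason to expect in-trial use to differ by arm. The assumed shift of 0.2 to 0.3 SD is small against about 0.89 SD, and section 3.11 uses the Mann–Whitney U test for non-normal data, which limits the pull of outliers. These points stand for the randomised contrast. They do not remove the loss of precision where the t-test is used, the possible influence of a few exposed samples in a small regression (not quantified here), or the possible bias against unrandomised controls.

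**Conclusion.** The point holds for the eligibility wording. The criteria in 3.3.2 (10) and 3.3.4 (3) reach only undefined regular use with no window, and they admit a patient or control who took a short course shortly before sampling. The consequence is added noise in the AG–WG microbiota comparison and the correlation analyses, and possible bias in the patient–control comparison, where no drug-use record is stated for the controls.

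The illustrated size depends wholly on the assumed exposure rates and the 2 to 3 SD shift; the documents give neither. Microbiota is a mechanistic outcome listed among the other outcome measures, and the ADAS-cog primary outcome is not directly affected. The change is a cheap improvement that should be made; the trial's main conclusion does not depend on it.

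**What to change.** 1. In 3.3.2 (10) and 3.3.4 (3), replace regular use with any use of probiotics, prebiotics or antibiotics within a pre-specified window before faecal sampling. The study team sets the length, and it is identical for patients and controls.
2. Extend the drug-use question in 3.8.5 to name these agents, including over-the-counter products, and ask it of controls at enrolment.
3. Flag any sample taken inside the window, and repeat the microbiota and correlation analyses without flagged samples.

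No treatment is withheld: a sample is flagged, or its collection delayed where possible. The cost is new wording in two criteria, a longer question already planned for patients and new for controls, one sensitivity analysis, and a few more screen failures or delayed samples.
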